**4. ESTIMATED DURATION OF THE STUDY**

5 years

**5. LAY LANGUAGE SUMMARY OR SYNOPSIS (no more than one paragraph)**

Authoritative parenting style has been associated with decreased obesity risk in children and can modify the delivery and impact of weight control strategies, making them more effective. At this time, gold-standard treatment for childhood obesity is family-based behavioral therapy (FBT). This treatment relies on behavioral strategies and the use of praise and a positive reinforcement system to change eating and activity behaviors, but does not target other aspects of parenting. Broadening parenting instruction to include effective limit-setting behaviors, parent-child communication, and authoritative parenting may increase parents' confidence and ability to successfully make behavior changes and modify the impact of the behavioral strategies being used. In this application, we propose to test the efficacy of a 6 month, 20-sessions, weight control program that combines traditional family-based behavioral therapy with comprehensive parenting training (FBT+PT) and compare it to traditional family-based behavioral therapy (FBT). We believe that there will be an additive effect of parenting training such that FBT+PT will have a greater effect on child weight loss (measured by BMI z-score) than traditional FBT. In addition we will measure parenting style, parenting strategies, behavioral strategies, and child factors (like impulsive behavior and temperament) to better understand the mediators and moderators of weight loss. These measures will be obtained by standard self-report measures and videotape encounters, allowing us to more objectively measure parenting dimensions. Clinical outcomes, like drop-out and acceptability, will also be assessed from the two treatment arms. The purpose of this study is to evaluate the effect of adding more comprehensive parenting training to traditional FBT. If successful, this program will be able to increase our ability to help children successfully lose weight.

**6. SPECIFIC AIMS**

Authoritative parenting style has been associated with decreased obesity risk in children and can modify the delivery and impact of weight control strategies, making them more effective. At this time, gold-standard treatment for childhood obesity is family-based behavioral therapy (FBT). This treatment relies on behavioral strategies and the use of praise and a positive reinforcement system to change eating and activity behaviors, but does not target other aspects of parenting. Broadening parenting instruction to include effective limit-setting behaviors, parent-child communication, and authoritative parenting may increase parents' confidence and ability to successfully make behavior changes and modify the impact of the behavioral strategies being used.

In this application, we propose to test the efficacy of a 6 month, 20-sessions, weight control program that combines traditional family-based behavioral therapy with comprehensive parenting training (FBT+PT) and compare it to traditional family-based behavioral therapy (FBT). The FBT+PT arm will incorporate more active

skills learning to increase adoption of authoritative parenting behaviors. We will recruit and randomize 160 overweight/obese children (BMI>85th percentile and <99.9th percentile) between 7 and 12 years old and their parent into a 6 month, 20-sessions FBT+PT or FBT program and follow them for 1 year post-treatment. The primary outcome is change in child body weight (BMI z-score). Our secondary aim will be to evaluate the effect of both treatments on drop-out rates, adherence, and acceptability. As an exploratory aim, we will evaluate parent and child level mediators and moderators of weight loss in each of the treatment arms in order to inform future treatment development. We will achieve the goals of this application by pursuing the following primary and secondary aims:

- **Primary aim 1:** Examine the efficacy of FBT+PT on child body weight compared to gold standard FBT. *We hypothesize that FBT+PT will show greater decreases in child body weight (BMI z-score) compared to FBT at post-treatment and 6- and 12-months post-treatment.*
- **Secondary aim 1:** Examine drop-out, treatment adherence, and acceptability in FBT+PT and FBT. We hypothesize that families randomized to FBT+PT will have lower drop-out rates, increased program adherence (including attendance, self-monitoring, use of praise), and higher ratings of acceptability.
- **Exploratory aim:** Examine mediators and moderators of weight loss in FBT+PT and FBT. We hypothesize that success will be *mediated* by actual change in parenting and behavioral skills, as well as self-efficacy to engage in behavior change. We propose that a) increased parent use of praise, b) effective limit-setting, c) decreased use of harsh parenting techniques, and d) increased behavior change self-efficacy will *mediate* the impact of the intervention on child weight status. We also hypothesize that a) sociodemographic factors (race/ethnicity, income, and education), b) baseline general parenting style, c) parent mental health status, and d) child responsivity to food cues will *moderate* treatment effects. Several factors (e.g., family functioning, chaos level, and child internalizing/externalizing behaviors) may act as both mediators and moderators of treatment effect and will be tested in both capacities.

In September 2017, we received an ancillary grant (R01DK114794), to examine reward and inhibition aspects of cognition, in both parents and children enrolled in this study (R01DK108686), in order to understand the factors that contribute to lack of response in family-based behavioral weight loss. The primary aims of the ancillary study are to determine behavioral and psychological phenotypes of reward and inhibition at baseline in parents and children and to evaluate whether the behavioral and psychological phenotypes at baseline predict weight loss in both parents and children at the 6-, 12- and 18-month timepoints. An exploratory aim is to evaluate whether the behavioral and psychological phenotypes identified at baseline in parents and children change over the measurement period and whether these changes are associated with weight loss.

## 7. BACKGROUND AND SIGNIFICANCE

The current gold standard treatment for childhood obesity is family-based behavioral therapy (FBT). This program provides the basic building blocks for weight management, including behavior therapy skills and nutrition and physical activity (PA) education. Children in these programs have shown a mean BMI z-score change of -10.3% (S.D. 9.2). However, not all children respond similarly to FBT, with only about a third of children able to maintain their weight loss over a ten year period. In addition, programs are often plagued by high drop-out rates, from 20% in academic research settings to 70% in clinical settings, impacting their efficacy. Therefore, studies are needed to determine how to optimize FBT for a greater proportion of families.

Cohort studies suggest that authoritative parenting, characterized by greater warmth/attachment and firm limit-setting, is associated with better weight outcomes. This authoritative parenting style may be important because it can alter the context in which behavioral strategies are implemented, thereby making them more effective. Furthermore, the use of praise has been associated with greater weight loss in the context of FBT, while permissive parenting is associated with poorer weight loss outcomes. Current FBT relies on behavioral strategies like self-monitoring, stimulus control, and problem-solving, but offers limited instruction on parenting, focusing only on the use of praise and positive reinforcement. Adding more comprehensive parenting training (that includes limit setting strategies and parent child communication skills) to FBT may increase the effectiveness of these programs. Ultimately, parents may become more confident to deliver weight control strategies and be able to do so in a more effective manner.

Parent training programs that focus on improving parent management techniques and parenting style have been successful at increasing parent use of supportive parenting and positive reinforcement techniques, decreasing harsh or permissive parenting, and increasing effective use of limit setting and other discipline strategies. Recent data suggest that a parenting program focused on weight loss can decrease child BMI z-score by 0.11 units in an Australian sample. However, this program offered little behavioral therapy and has never been compared to traditional FBT. At this time, it is unclear whether adding more comprehensive parenting training to traditional FBT can increase changes in child body weight compared to traditional FBT.

## 8. PROGRESS REPORT

N/A

## 9. RESEARCH DESIGN AND METHODS

Research design: We will enroll an estimated 350 parent-child dyads to treat at least 160 parent-child dyads and randomize them into a 6 month, 20 session traditional FBT or FBT+PT. Families will be followed for 12 months post-treatment, making the total length of participation 18 months. Randomization will be conducted with a random number generator independent of the investigators. All children will be randomized by gender and randomization will be monitored throughout the proposal to determine whether any systematic differences in demography (age, race/ethnicity) or BMI% become evident. Treatment will take place at CHEAR in La Jolla or San Marcos, or remotely via password protected ZOOM meetings. Families randomized to FBT will take part in traditional 20-session group therapy for children and parents that includes nutrition/PA education as well as behavioral therapy components. Groups will include didactic sessions and problem solving. Families who are randomized to FBT+PT will participate in a 20 session program that focuses on teaching positive discipline strategies and effective parenting skills in addition to the components covered in traditional FBT. The process in these groups will include videotape modeling, role plays, and rehearsal (active skills training). Child groups will cover nutrition/PA information and basic behavioral strategies. Since the main difference between FBT+PT and FBT is the parenting training component, and it is not appropriate to introduce parenting issues to the children, the content of child groups will not differ between treatment arms. Once treatment is complete, families will be followed for one year post-randomization. Assessments will occur at baseline, post-treatment (6 months), and 6- and 12-months post-treatment/follow-up. Assessments will include height and weight data obtained during the study period, self-report measures, and videotaped family meals. All assessments that need to be conducted via virtual meetings will be conducted using password protected ZOOM meetings.

Treatment elements: Both treatment arms will consist of 20 weekly group meetings for parents and children. Parent group meetings will last 90 minutes each week and discuss principles of behavior change, nutrition and physical activity. Children will also meet in a separate group at the same time and discuss nutrition and physical activity topics that correspond to the parent meetings. Both parents and children will receive weekly manuals and activities to do at home. The purpose of the manual is to provide key components of family-based behavioral treatment to the families and reinforce what is being taught in groups. Child manuals will provide similar content as the parent manual but be developmentally appropriate for children age 7-12 years old. Parents will also be asked to meet daily with their child to discuss/monitor eating and activity behaviors and other aspects of the program. Parents will be expected to report back on their experiences the following week.

Additional parenting strategies will be addressed in FBT+PT and active skills training used to reinforce these behaviors and parenting style. The parenting training component will be adapted from The Incredible Years Program (IYP). This program is based on social learning models of parent-child interaction and encourage parents to use emotionally supportive behavior and assertive discipline techniques (rather than coercive or negative reinforcement techniques) when interacting with and educating their children. Parents learn how to *use positive reinforcement strategies, use more effective discipline strategies, improve communication techniques, learn how to monitor child behaviors, regulate their own emotions, and problem solve*. This program uses active skills training (e.g. *video modeling, role play and behavioral practice in class, group discussions and problem-solving, and emotion regulation training*) to increase skills adoption. Using these techniques, parents can observe others interacting with children in ways that promote positive behaviors

and can practice “doing it right”. This method allows parents to gain greater insight into the impact of their behaviors, receive immediate feedback, has been shown to be effective at producing behavioral changes, and is not currently used in traditional FBT.

During the first half of each session in FBT+PT, group leaders will address basic behavioral, nutrition, and PA information similar to what is addressed in FBT. Parenting strategies will be introduced and practiced during the second half of the session. Two-minute parenting skills vignettes that demonstrate positive and negative parent-child interactions will be shown by group leaders and discussed with parents. These vignettes have been developed by IYP and are available for purchase. Vignettes that model parents interacting with their child in food and PA situations will be emphasized. After viewing each vignette, parents will discuss what they have seen and practice the targeted skills, receiving feedback from group leaders and other parents. All parents will be expected to role-play during group to help increase mastery of the parenting skills. Parents will problem solve with the group while also learning how to self-manage their thoughts, emotions, and behaviors. Group leaders will reiterate the principle parenting technique that is being addressed and discuss how to use these techniques in different family situations to help increase generalization of the behavior. After each session, parents will also be given assignments to practice these skills at home. At the end of these types of programs, parents often feel more competent to engage in these newly practiced parenting behaviors and learn how to self-monitor their emotions and behaviors, cope with challenges, and seek appropriate support when needed. This more interactive format has been successful at decreasing the use of harsh discipline and critical statements and increasing supportive parenting, displays of affection, and praise.

*Quality Control for Treatment:* Close monitoring through multiple methods will be used to ensure treatment integrity. Interventionists (FBT+PT, FBT) will attend full day trainings with Drs. [name], [name] and [name]. All interventionists will meet weekly with a licensed clinical psychologist in separate supervisions. Intervention sessions will be audiotaped for ongoing performance monitoring. Random samples (e.g., 20% or more) of all intervention sessions will be rated for fidelity by an independent rater using a measure created for this study. Tapes will be destroyed within three years of completion of the study.

### **Measures:**

Data from the child and the parent will be obtained specifically for research purposes. Data will be collected at 4 time points (baseline, post-treatment (6 months), and 6- and 12-months post-treatment). Assessments will be completed either in-person at the CHEAR office or in a password protected ZOOM meeting. The baseline assessment will include 3 approximately three-hour visits for the child and parent. At the baseline assessment, parents and children will complete surveys and be weighed and measured. Children will also wear an accelerometer for 7 days. Parents and children will be scheduled to complete a videotape family meal at their home. Following the first assessment visit, parents will be given the option of completing some surveys via the secure-web-based survey format prior to attending the in-person visit to reduce the amount of time they need to be present at CHEAR. If parents do not complete the surveys in advance, they will complete them as part of the visit. All surveys provided to be completed at home will include information that does not warrant immediate follow-up (i.e., no questions about suicidal ideation or self-harm). All surveys will be identified with the unique study ID rather than any identifying information. The assessments at follow-up time points (post-treatment (6 months), and 6- and 12-months post-treatment) will be similar to the baseline assessments and will consist of 2 approximately three-hour visits for the child and parent. In addition, families be offered the option of one additional assessment visit (similar to baseline) at post-treatment (6 months), and 6- and 12-months post-treatment, in order to evaluate the aims of the ancillary study. This visit will involve an additional consent form and additional compensation.

Weights will be obtained throughout the treatment program and heights will be obtained at the mid-treatment, post-treatment, and 6- and 12-months post-treatment assessment. The full battery of surveys, accelerometer data, dietary questions, and videotape assessment will occur again at post-treatment and 6- and 12-months post-treatment. A saliva sample for genetic material will only be obtained at baseline. A stool sample for microbiome analysis will be obtained at all time points. A full list of measures and assessments are listed in table 1.

a) Anthropometry. Both child and parent will have their body size measured. Height will be measured using a portable Schorr height board in duplicate; body weight will be measured on a Tanita Digital

Scale (model WB-110A) in duplicate. The average of the two values will be used for analysis and will be translated for children to BMI for age percentile score using the CDC growth charts and to Body Mass Index (BMI) in parents ( $BMI=[kg/m^2]$ ). Children with a BMI  $\geq 85^{th}$  percentile and parents with a BMI  $\geq 25$  will be considered overweight.

- b) *Dietary intake.* Dietary intake of the child will be assessed with dietary knowledge questionnaire, which will assess eating habits of the children and the parents.
- c) *Physical activity.* Physical activity of the child and parent will be assessed using Actigraph accelerometers. Actigraph accelerometer (model GT1M, [www.theactigraph.com](http://www.theactigraph.com)) is a small (3.8 x 3.7 x 1.8 cm), lightweight (27 g), uni-axial accelerometer that is worn on a belt snugly around the waist. The GT1M records time varying accelerations ranging in magnitude from approximately .05 to 2 G's. We plan to ask participating children to wear the Actigraph for 7 consecutive days so that we may be able to assess within-person variation more precisely than if we collected data for only 4 days. Trained staff will instruct participating children and their parents on the proper procedure for attaching the Actigraph to their waistband and completing a log to record the times they did not wear the Actigraph (they'll be asked to remove the actigraph during sleeping time).
- d) *Sedentary behaviors & recreational media use.* Sedentary behaviors and media use will be assessed using an instrument developed in the PACE+ Adolescent trial. Both child and parent will complete this measure. This 8-item survey was based on a survey developed by Robinson and measures hours spent doing various sedentary behaviors during a typical school day and non school day. Analysis of the survey indicated that 3 factors account for 58% of the variance. The three factors were "Idle" (TV, computer/video games, listening to music, talking on the phone), "Intellectual" (homework, reading), and "Creative" (playing musical instrument, arts and crafts).
- e) *Activity logs.* In addition to wearing the actigraph for 7 consecutive days, children and parents will complete activity logs that include physical activity and sedentary activity. Children will record their activity, television usage and computer usage on specific activity logs for the assessment. When children and parents receive instructions on using the actigraph, they will also receive instructions on completing activity logs. Actigraphs's and activity logs will be returned to project staff at the first treatment session.
- f) *Demographics characteristics and Weight History (Baseline only).* Parent and child will complete separate demographic questionnaires that includes items on personal weight history, types of weight management strategies, dieting, weight fluctuation, health history, and parents will complete a locator information for assistance in tracking individuals.
- g) *Videotape measures* will be used to obtain objective measures of parenting. Families will be videotaped eating a meal together, in their home, at baseline, post-treatment, and follow-up. Only immediate family members living within the household will be invited to participate in this recording, and no additional guests will be allowed. The research team has experience collecting data in this method and has a standardized protocol for the taping and coding of **mealtime feeding behaviors** (see Appendix). This schema captures behavioral therapy strategies such as portion control, stimulus control, modeling, and monitoring used in a feeding situation. Additional coding schemas to be use are the **Coder Impression Inventory (CII)** and the **Mealtime Family Interaction Coding System (MICS)**. The data from these tapes will be used for research purposes only. Only [name], her trained research staff and collaborators will have access to these de-identified tapes.
- h) *Executive functioning (EF: child and parent).* *Attentional control, cognitive flexibility, working memory, and general cognitive abilities* will be measured by the Flanker Inhibitory Control and Attention Test, Dimensional Change Card Sort Test (DCCS), Picture Vocabulary Test, Picture Sequence Memory Test, Verbal List Learning Task with Food, Digit Span, Attention Bias Task, Relative Reinforcing Value of Food, and Oral Reading Recognition Test. *Inhibition* to food and non-food cues will be measured by the *stop signal task-food version*. On each trial, participants are asked to discriminate between a picture of calorically-dense food or neutral object (e.g, chair). The two primary outcomes, stop signal reaction time for food pictures (SSRT-food) and neutral pictures (SSRT-neutral) will be compared to assess for food-specific impulsivity versus general impulsivity. *Overall child EF* will be measured by the Behavior Rating Inventory of Executive Function – Parent Report (BRIEF-2), which is completed by the parent. This 63-item form contains three indices, nine clinical scales, and three validity scales. *Overall parent EF will be measured by the* Behavior Rating Inventory of Executive Function—Adult (BRIEF-A), to be completed by the parent. This 75-item form contains nine clinical scales and three validity scales.
- i) *Psychophysiological Measurements.* All of the psychophysiological measures were chosen as measures

of Cephalic Phase Responses (biological preparatory responses to food) and have shown sensitivity to conditioning paradigms with food. Cephalic Phase Responses (CPRs) have been associated with responses to food and perceived craving in humans and differentiate overweight and normal weight adults. Electrophysiological recordings will all be sampled at 250 Hz. Participants will be exposed to highly palatable food for 6 minutes and a neutral object for 2 minutes.

j) Parenting (child and parent). A component of the study assessment procedures will include a battery of reliable and valid measures of parenting, including The *Child Report of Parent Behavior Inventory*, the *Comprehensive Feeding Practices Questionnaire*, and The *Consideration of Future Consequences Scale*, *Comprehensive General Parenting Questionnaire*, *Birch Child Feeding Questionnaire*, *Parent Importance Confidence and Readiness Questionnaire*, *Parent Motivation Inventory*, *Family Adaptability and Cohesion Scale IV*.

k) Treatment adherence (child and parent). Adherence to recommendations (e.g. goal setting, stimulus control, contracting) and self-monitoring (% days monitored) for child and parent will be collected using standard study assessment tools to assess treatment adherence. All self-monitoring will be scored for number of days that participant monitored any meals or snacks and for number of days that participants monitored all meals or snacks (as defined by three, time distinct entries for meals and at least one snack). Parents and children will also complete treatment adherence questionnaires that query how many days they self-monitored immediately after meals, how many days they self-monitored at the end of the day, and how accurate they perceive their own self-monitoring to reflect actual intake.

l) Treatment acceptability (child and parent). Questionnaires will assess parent and child liking and any concerns or barriers to implementing the gshFBT or the FBT treatment.

m) Gut microbiome: Participants (parent and child) will be sent a stool collection kit and asked to provide a stool sample within 24 hours of their pre- and post-treatment assessment visits. The BBL CultureSwab will be used to collect samples from subjects (Becton-Dickinson catalog #BD281130) from tissue paper. These swabs have been used successfully by the [name] lab, who has shown that microbiome analysis using these swabs was comparable to that using more traditional stool collection methods. De-identified stool samples will be stored at -20°C. Microbiome analysis will be conducted to examine the relationship between changes in weight and gut microbiome.

n) Genetics. Parent and child will each give a saliva sample which will be collected using the Oragene•DNA saliva collection system. Samples will be collected before the first treatment session. Saliva will be obtained, stored at room temperature using the deidentification number assigned to each patient, and banked for later analysis. Genetic data will be used to examine the relationship between target SNPs and eating behaviors. Disease specific susceptibility genes will not be examined. Data is for research purposes only and subjects will not be informed of the results of their genetic testing.

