solving, self-monitoring) at the end of treatment are related to greater decreases in BMIz over time ('b' paths) (Exploratory Aim). The product of these sets of coefficients and associated standard errors will provide effects used to test statistical significance. Mplus 6.12 includes both normal theory and bootstrap methods for estimating both total indirect (all mediators) and specific indirect effects for each proposed mediator. For the moderator hypotheses tested as part of the Exploratory Aim, the models used for the primary aim will be augmented by including a coefficient for the main effect of the moderator (e.g., parent mental health, baseline general parenting style, child food-cue responsiveness) and interactions with treatment and time.

For the Ancillary study:

**Primary aim 1: To determine behavioral and psychological phenotypes of reward and inhibition at baseline in parents and children:** Latent Profile Analysis (LPA) will be used to derive empirically defined groupings of participants based on common patterns of responses to hypothesized inhibitory control (behavioral motor, emotional regulation, and memory for food), reward function (normed physiologic reactivity, self-reported reward responsiveness), and cognitive bias (attentional bias, Stroop bias) indices of risk via maximum likelihood estimation. Models will be estimated with numbers of classes determined iteratively using the Lo-Mendell-Rubin Adjusted Likelihood Ratio Test (LMRT), the Bootstrapped Likelihood Ratio Test (BLRT), Akaike information criteria (AIC), and sample size-adjusted Bayesian information criteria (BIC). In addition to these indices, each model will be evaluated using interpretability of identified conditional means to protect from spurious classes based upon nonnormal distributions.

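### The complete-day self-monitoring score requires a snack entry, so a fully recorded day without a snack counts as incomplete for any child or parent in either arm

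*Protocol*

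**What the plan says.** Section 9, Measures, item k scores self-monitoring, for child and parent, in two ways. The first is the "number of days that participant monitored any meals or snacks". The second counts days on which participants "monitored all meals or snacks (as defined by three, time distinct entries for meals and at least one snack". The text gives no exception for a day without a snack and mentions no way of recording that none was eaten. A separate questionnaire asks participants "how accurate they perceive their own self-monitoring to reflect actual intake", but the answer does not enter the definition of a complete day. Table 1 names weekly habit books as the source.

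Self-monitoring is used in two places. Secondary aim 1 (section 6) hypothesises that FBT+PT will show "increased program adherence (including attendance, self-monitoring, use of praise"). The Analysis text also gives it as an example of a mediator, asking whether changes in skills such as problem-"solving, self-monitoring) at the end of treatment are related to greater decreases in BMI" z-score. Neither place says which of the two scores will be used.

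**The concern.** The score is labelled as monitoring of all intake, but its definition can fail when all intake was monitored. Two days show the mismatch:

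- Three meals eaten, no snack eaten, all three meals recorded: recording is perfect, and the day is scored incomplete.
- Three meals and several snacks eaten, the meals and one snack recorded: recording is incomplete, and the day is scored complete.

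The punctuation leaves some doubt about how many entries are meant, but a snack is required on either reading. This is a rule that the protocol fixes, not a detail left open.

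At stake is one component of the adherence comparison in Secondary aim 1. If this score is the one used as a mediator, the exploratory link between monitoring and weight change is also affected, because a participant who stops snacking can look less adherent with unchanged recording.

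**Working it through.** The protocol states no target, power or expected value for this score, so there is no figure to reproduce. The check is the logic of the definition plus simple arithmetic.

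**Inputs**

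- The rule: three time-distinct meal entries and at least one snack (section 9, item k).
- t, the true share of days on which everything eaten was recorded: not given; assumed 70%.
- f, the share of those fully recorded days that were snack-free: not given; assumed 10% to 30%.
- Monitoring period: 20 weekly meetings (section 9), so 20 x 7 = 140 days if recording is daily (assumption).

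The formula takes three meals as eaten on each fully recorded day. It counts only the downward error; days that pass with some snacks unrecorded push the score up and are not quantified here.

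**Level of the score.** Scored rate = t x (1 - f).

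| f | Scored rate at t = 70% |
|---|---|
| 0% | 70% |
| 10% | 0.70 x 0.90 = 63% |
| 20% | 0.70 x 0.80 = 56% |
| 30% | 0.70 x 0.70 = 49% |

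**Arms with equal f.** With equal t the scored difference is 0. A true difference shrinks by the factor (1 - f): 5 points become 4.5, 4.0 or 3.5 at f = 10%, 20% or 30%.

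**Arms with different f and equal t.** Spurious difference (FBT+PT minus FBT) = -t x (f in FBT+PT - f in FBT).

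| f in FBT | f in FBT+PT | Spurious difference at t = 70% | Over 140 days |
|---|---|---|---|
| 10% | 10% | 0 | 0 |
| 10% | 15% | -3.5 points | -4.9 days |
| 10% | 20% | -7.0 points | -9.8 days |
| 10% | 30% | -14.0 points | -19.6 days |

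The sign reverses if the snack-free share is higher in FBT: 20% in FBT and 10% in FBT+PT gives +7.0 points.

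**Point of cancellation.** Take a true advantage of 75% in FBT+PT over 70% in FBT, with f = 10% in FBT. FBT scores 0.70 x 0.90 = 63%. FBT+PT scores the same when 0.75 x (1 - f) = 0.63, that is f = 1 - 0.63/0.75 = 16%. A gap of 6 points in snack-free share then hides a true 5-point advantage.

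**The case against.** A reader might infer that the rule penalises FBT+PT, because that arm practises limit-setting in food situations and could therefore reduce snacking more. The protocol does not support stating this as fact. It says that "the content of child groups will not differ between treatment arms", and that for FBT+PT parents "group leaders will address basic behavioral, nutrition, and PA information similar to what is addressed in FBT". Nowhere does it say that one arm targets, or is expected to achieve, less snacking. A route through limit-setting is possible, but it is conjecture, and the direction and size of any arm bias are unknown.

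Other points limit the reach of the concern, and they stand:

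- The any-entry score needs no snack, and the questionnaires add further information on monitoring.
- Section 6 names praise, limit-setting, harsh parenting and self-efficacy as the hypothesised mediators. Self-monitoring appears only as an example in the Analysis text.
- The layout of the habit book is not shown, so it may already have a place to write that no snack was eaten. The scoring rule as worded would still not count such an entry as a snack.

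It can also be argued that requiring a snack entry is a deliberately strict screen against records that leave snacks out. That is a fair aim, and it is why simply dropping the condition is a poor replacement: days on which every snack went unrecorded would then pass. It does not justify failing a day that was recorded in full. Nor can the any-entry score stand in for completeness, since a single recorded item satisfies it.

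**Conclusion.** The concern holds as a misclassification in the stated rule. A fully recorded snack-free day is scored incomplete for children and parents in both arms, and the complete-day rate is understated by the factor (1 - f). Under the assumed 70% true rate and f of 10% to 30%, it would read 63% to 49%.

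For the comparison of arms the conclusion is conditional. Equal snack-free shares produce no false difference and only dilute a true one. Unequal shares bias the comparison, by 7 points in the 10% v 20% example, in whichever direction the shares differ. Every rate used here is an assumption, and a claim that FBT+PT in particular is disadvantaged goes beyond the document.

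The scope is narrow: one of two self-monitoring scores, within one component of a secondary aim, and possibly an exploratory mediation analysis. The any-entry score and the primary BMI z-score outcome are untouched. It merits correction because the rule contradicts its own label and the remedy is cheap.

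**What to change.** In section 9, Measures, item k, define a completely monitored day as one with three time-distinct meal entries and either at least one snack entry or an explicit 'no snack today' mark in the habit book. Keep the any-entry score as it is. Where every fully recorded snack-free day carries the mark, the scored rate no longer depends on f: in the illustration above, 70% stays 70%. Days with several snacks and only one recorded would still pass; the mark does not cure that.

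For books already collected without such a mark, report days with three time-distinct meal entries as a sensitivity score beside the current rule, and note that it passes days with unrecorded snacks. It should not replace the current rule, because it exchanges one misclassification for another.

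The cost is one tick box in the habit book and a small amount of rescoring.
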